### Trial monitoring

No regular external trial auditing is scheduled. However, trial monitoring personnel include a safety officer (SO) appointed by the funding body (NIH) and the two PIs, [name] (PI) and [name] (MPI). Study staff and the PI will review information regarding safety, data quality, and validity on a weekly basis, informing the MPI immediately of any concerns. All data related to recruitment, screening, enrollment, baseline measurement, and intervention measurement will be reviewed weekly by the PI. Data collected from enrolled participants will be reviewed weekly by the statistician with the PI. Additional investigators and study staff will be asked for their input or expertise as needs arise. If unforeseen hazards or risks are identified that may lead to serious adverse events, the PI consults the appropriate members of the team, including the NIH-appointed SO.

### Adverse event monitoring and reporting

Participants randomized to the CON group are asked to report adverse events at the beginning of each week during the SOC period using the MyCap application, a mobile application version of REDCap that participants install on their smart phone devices. Once these participants engage in the intervention (one-way crossover period) they report adverse events on the same schedule as the EXP group. Participants randomized to the EXP arm complete adverse event reporting each time we see them (2x per week) via REDCap. With respect to the adverse event of falls, participants are asked about the incidence of falls and loss of balance. Researchers review REDCap responses once per week for the CON participants within the SOC period and prior to the start of Tango lessons for participants engaging in the Tango intervention (EXP and crossed over CON). If an adverse event is reported, the PI is notified. Classification of the events as Serious or not occurs within 24 hours.

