## Methods

### Study Design

This is a multi-center, prospective randomized controlled study of superiority between an experimental intervention and usual care control arm. Eligible participants who provide informed consent will be randomly assigned to the Tango experimental (EXP) or the standard of care (SOC) control group (CON) in a 1:1 ratio. The study primary endpoints are changes from baseline to 4 weeks of intervention in the patient-reported outcome (PRO) of the sensations of numbness and/or tingling (Aim 1) and the quantitative outcome of dual task function during performance of a cognitive challenge simultaneously with a walking task (Aim 2). As an exploratory endpoint, we will assess the effect of Tango on the blood-based biomarkers that potentially mediate sensation and function as well as on cognitive load during a dual-task paradigm as measured by brain activity (i.e. high gamma) (Aim 3). Tables 1 & 2 present the data collection schedule for the EXP and CON groups, formatted per the Standard Protocol Items: Recommendations for Interventions Trials (SPIRIT) recommendations (43–45). Figure 1 illustrates the overall study design as a flow diagram. As detailed in Tables 1 & 2, outcomes are assessed at the following timepoints: repeated baseline (Baseline), primary endpoint (4 weeks of intervention or SOC), 8 weeks of intervention, 12 weeks (follow-up after a 4-week period of no structured intervention being offered), and weekly for 6 months following intervention end. Secondary outcome measures include clinical and biomechanical tests of function and patient-reported outcomes that complement the primary outcome measures in addition to falls incidence. Tertiary outcome measures, listed in Table 3, include within-session effects, satisfaction collected at session end, and surveys used to inform monitoring and shaping of interventions including Rating of Perceived Exertion - Physical (RPE-P; 6–20 scale), Rating of Perceived Exertion - Mental (RPE-M; 6–20 scale), and Intrinsic Motivation Inventory (IMI). To support beneficence, individuals randomized to the control arm will be given the option of participating in the experimental intervention after primary outcomes measurement.

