###### Falls tracking:

Falling is defined as an unexpected loss of balance in which an individual comes to rest at a position lower than before the unexpected event (74). We elicit self-report of falls and loss of balance using the question “How many times have you fallen or felt like you lost your balance since we last saw you?” Responses are typed by the participant and reviewed for incidence of falls, incidence of loss of balance, and details offered about either incidence. During the 6-month follow-up period after intervention end, each participant will use the MyCap application to report falls weekly.

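### In the four randomized weeks, falls and adverse events are asked about twice a week in EXP but once a week in CON, with different recall windows, which may modestly distort the falls comparison

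*Protocol article*

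**What the plan says.** All places are in the protocol article.

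- **EXP schedule** (Adverse event monitoring and reporting): EXP participants "complete adverse event reporting each time we see them (2x per week) via REDCap".
- **CON schedule** (same section): during the SOC weeks, CON participants are "asked to report adverse events at the beginning of each week during the SOC period using the MyCap application". After crossover, "they report adverse events on the same schedule as the EXP group".
- **Staff review** (same section): "Researchers review REDCap responses once per week for the CON participants within the SOC period and prior to the start of Tango lessons".
- **Falls belong to this reporting** (same section): "With respect to the adverse event of falls, participants are asked about the incidence of falls and loss of balance".
- **Falls item** (Falls tracking): "How many times have you fallen or felt like you lost your balance since we last saw you". After the intervention ends, every participant reports falls weekly in MyCap.
- **Role of falls** (Study Design): secondary outcomes include "patient-reported outcomes that complement the primary outcome measures in addition to falls incidence".
- **Randomized period** (Statistical analysis): the randomized comparison ends at week 4.
- **Tables 1 and 2**: both arms have a week-4 assessment of adverse events including falls.
- **Table 3**: footnote a sets recall to the shortest of the last week, the time since last seen, or the time since last answering. In the adverse-events row it is attached to baseline and Tango sessions. As read here, that row has no mark in the weekly SOC column, although the control-intervention section and the adverse-event section both describe weekly reporting by app.

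**The concern.** The two arms are asked about the same events on different schedules in exactly the weeks when they can be compared as randomized. After crossover the schedules match, and in the follow-up period everyone uses the same weekly app form, but by then CON has also been offered Tango.

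Participants are enrolled because of a balance deficit, so falls are a natural safety and benefit question for a dance intervention. The falls item also counts a felt loss of balance, a minor event that is easily forgotten. If shorter recall and more frequent prompting record more such events in EXP, Tango could look less safe than it is, or a real reduction in falls could be diluted. Analysis cannot readily repair this. Adding two half-week EXP reports gives a count for the week, but not the count that a single 7-day recall would have produced.

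**Working it through.** The plan states no fall rate, adverse-event rate or capture rate, so it has no figure of its own to reproduce. The check is a count from the text, followed by a sensitivity range on stated assumptions.

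**1. Prompts in the randomized weeks (from the text)**
- EXP: 4 weeks × 2 = 8 prompts, mean gap 7/2 = 3.5 days, if every session is attended.
- CON: 4 weeks × 1 = 4 prompts, gap 7 days.

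Both sets of windows can cover the same 28 days. With perfect recall, frequency alone would not change the counts. Any distortion must come from recall length, prompting or the wording of the window.

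**2. Recall loss (assumed model)**

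Assume that an event falls at a uniformly random time in a window of L days and that memory of it decays exponentially with half-life H. With k = ln 2 / H, the captured share is

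capture(L) = (1 − e^(−kL)) / (kL).

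Example with H = 7, so k = 0.099:
- EXP: kL = 0.347, capture = (1 − 0.707)/0.347 = 0.845.
- CON: kL = 0.693, capture = (1 − 0.500)/0.693 = 0.721.
- Apparent ratio with no true difference: 0.845/0.721 = 1.17.

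| Half-life (days) | EXP capture | CON capture | EXP:CON ratio |
|---|---|---|---|
| 7 | 0.845 | 0.721 | 1.17 |
| 14 | 0.918 | 0.845 | 1.09 |
| 28 | 0.958 | 0.918 | 1.04 |
| 56 | 0.979 | 0.958 | 1.02 |
| no forgetting | 1.000 | 1.000 | 1.00 |

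**3. Effect on a test of falls (assumed rates and test)**

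Take 50 per arm, the number the plan aims to retain. Assume Poisson counts and a two-sided 5% Wald test on the log rate ratio. Let λ be the recorded falls per CON participant over 4 weeks, c = 50λ, e = c·r, and t = ln r / √(1/c + 1/e). The false-positive rate is Φ(t − 1.96) + Φ(−t − 1.96).

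Example with λ = 0.3 and r = 1.2: c = 15, e = 18, t = 0.182/0.350 = 0.52, rate = 8.2%.

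| λ | r = 1.0 | r = 1.1 | r = 1.2 |
|---|---|---|---|
| 0.1 | 5.0% | 5.3% | 6.0% |
| 0.3 | 5.0% | 5.8% | 8.2% |
| 1.0 | 5.0% | 7.8% | 15.9% |

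The effect is small unless recorded events are frequent, which is more plausible for loss of balance than for falls proper.

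**4. Does the shared week-4 visit cure it?**

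Not clearly. The falls item refers back to the last time the participant was seen. For EXP that is the previous class, a few days earlier. For CON, whose reporting in between is remote, it may be the whole SOC period. The shortest-window footnote would help, but it is not shown against a weekly SOC entry for adverse events.

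**The case against.** Much of the case on the other side stands.

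- **Mode.** A reader might infer a contrast between staff interviews and an app. The article does not support that: participants complete the surveys themselves, type their own falls responses, and use electronic REDCap forms in both arms, MyCap being the mobile version. What remains is the difference in frequency, recall span and occasions for staff follow-up.
- **Scope.** A reader might infer that a planned between-arm test of all harms is compromised. No such test is stated for adverse events other than falls, so for these the issue is only whether reported rates are comparable. How falls are counted and tested may be set out in the full protocol or analysis plan.
- **Size.** A reader might choose capture rates freely, for example 90% against 70%, and infer a ratio of 0.90/0.70 = 1.29. These rates are not in the documents. Under the forgetting model above, 70% capture at 7 days implies about 83% at 3.5 days, a ratio of 0.83/0.70 = 1.19.
- **Direction.** A reader might infer that Tango is bound to look worse. That is not certain. EXP is asked only when seen, and the section on barriers to participation expects missed sessions, so someone who falls and stays away is not asked that day. In CON, a question about the time since last seen, answered weekly by app, could lead to the same fall being entered more than once.
- **Monitoring.** Asking before each class is reasonable safety practice. The point is not to stop it, but to keep it out of the between-arm comparison.

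None of this removes the unequal schedule, which the article states outright.

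**Conclusion.** The point holds in a limited form. In weeks 0 to 4, EXP is asked about falls and adverse events twice as often as CON (8 prompts against 4), and the falls item looks back over a span that differs by arm. The comparison of falls incidence, and the descriptive comparability of adverse-event rates, may therefore be modestly distorted.

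The size cannot be derived from the documents. The range of about 1.02 to 1.17 rests on exponential forgetting with an assumed half-life of 56 to 7 days, full attendance and equal true rates. With no forgetting the ratio is 1.00. Over-capture in EXP is the likelier direction, but the opposite is possible. The stronger statement, that the comparison is biased against Tango by a known amount, is not supported. The two primary outcomes, the primary estimand and the sample size are not affected. This is a cheap improvement, not a threat to the trial's main conclusions.

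**What to change.** 1. In weeks 1 to 4, give both arms the same once-weekly MyCap form for falls and adverse events, with a fixed window of the past 7 days in place of the time since last seen.
2. State that the between-arm comparison of falls in the randomized period uses this form only.
3. Keep the per-class questions in EXP, for safety monitoring alone.
4. Reconcile the adverse-events row of Table 3 with the control-intervention and adverse-event sections. Check the typeset table first, in case a mark in the weekly SOC column was lost when the text was read.

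**Cost.** One short extra form per week for EXP, at most 70 × 4 = 280 forms at the planned 70 per arm, in an app that all participants use later for follow-up. The trial has been open since January 2025, so this needs an amendment with NIH and IRB approval. Participants enrolled before the change will lack the common form, and their falls data should be shown separately. With enrollment expected to run to December 2028, an early change would cover most of the sample.

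**Limit.** The per-class questions may still prime EXP participants when they answer the weekly form. The change reduces the difference in ascertainment but does not abolish it.

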#### Serious adverse events

All serious adverse events are immediately reported to the research team and PI and then reported to the IRB, sponsor, and SO within 24 h.

#### Nonserious adverse events

Any nonserious adverse events are reported to the SO in biannual meetings and are subject to review prior to receiving authorization for the continuation of the research.

#### Biannual reports

A biannual open report summarizing study progress and safety monitoring data is reviewed by the SO and representatives from the NIA/NIA. Approval of the SO is required for the trial to continue.

#### Post-trial care

Both Tango and SOC participants continue to report adverse events and CIPN EMA for 6 months post-intervention. Researchers monitor responses and check in with participants as needed. Upon completion of the 6-month follow-up period researchers communicate their appreciation for participation.

### Protocol amendments

Any changes to the protocol require written amendments that must be approved by the NIH and IRB. Upon acceptance from the sponsor and IRB, the PI makes updates to the study record published on ClinicalTrials.gov. If the PI determines that a protocol deviation is necessary for safety reasons, scheduling, recruitment, or personal accommodations for participants, the IRB will be notified immediately.

### Confidentiality

Any physical documentation containing protected health information is stored in a locked cabinet located within research or clinical designated space that is locked and/or monitored when not occupied. Digital documentation is stored in REDCap and/or on secure servers requiring password authentication that are behind secure firewalls.

### Access to data

Study staff, OSU IRB, and representatives of the NIH have access to study data. All those who have access to study data are trained in HIPAA standards for privacy protection and do not refer to confidential information with anyone outside of the study team.

### Dissemination policy

The results of our research will be disseminated to (a) the scientific community; (b) breast cancer survivors; (c) persons with symptoms of neuropathy; (d) participants of the trial who wish to view their data after the 5-year study is complete; and (e) the public. The results of this research will be presented at scientific conferences, including the Multinational Association for Supportive Care in Cancer (MASCC), American Congress of Rehabilitation Medicine (ACRM), and American Society of Biomechanics (ASB). Additionally, results will be published in peer-reviewed journals.

## Discussion

As BC survival rates improve due to available treatments such as chemotherapy, the long-term quality of life for survivors has become a crticial focus of care. The rationale for this study stems from accumulating evidence that PA represents a viable non-pharmacologic avenue to treat one debilitating symptom of survivorship: chronic CIN (6, 17, 25). As a candidate form of neurologic dance training, Tango has been demonstrated to improve quality of life in populations with neuropathology (38, 46, 54). The scientific premise of this study is that Tango stands to achieve more gains than the current medical SOC for CIN by combining PA with rhythmic musical engagement and delivering the intervention in a socially-engaged environment. Based on previous data establishing safety, feasibility, and initial effect of Tango for survivors with CIN (38, 46), we have designed a randomized controlled trial to compare the effectiveness of the SOC versus an experimental arm that delivers Tango. We assess comparative effectiveness in terms of patient-reported, functional, and neurophysiologic outcomes relevant to BC survivorship. Our findings may lead to a safe, effective, simple, economical, non-pharmacologic intervention that improves CIN-related deficits and symptoms through activity that can be performed with a friend or loved one. Adding small doses of NDT as standard of care (SOC) for survivors with CIN is a simple, cost-effective solution that can be implemented anywhere in the world without major regulatory hurdles. Better functional recovery for survivors with CIN will lead to improved quality of life, short-term, and long-term health and wellness outcomes for these individuals. Therefore, the risks that participants in this study might incur are minor relative to the potential benefits of improving symptoms and function for BC survivors with CIN and measurable balance deficits.

### Trial status

This study has been active and open for enrollment since January 17th, 2025. Enrollment is expected to be completed by Dec 2028. Intervention delivery and follow-up are expected to be completed by July 1st, 2029. The clinical trial number associated with this trial is NCT06749210.

## Figures and Tables

**Figure 1 F1:**
[figure not shown]
Flow chart of study design from screening through the follow-up (f/u) period with assessments indicated throughout. Postural control data will be taken at each Tango session in addition to all assessment periods. Each assessment timepoint may contain 1) clinical measures: PROs, dual-task function, and upper extremity function; 2) biomechanical measures: postural control and gait stability; and 3) exploratory measures: biomarker and EEG sampling. For more detailed information, refer to tables 1 & 2. Processing of data will happen after the conclusion of the follow-up period per participant. Analysis of the primary outcome measures will be conducted after all data has been collected.

**Table 1 T1:** SPIRIT report of intervention effect outcome measures for EXP group.

	Study Period						
	Enrollment		Allocation	Post-Allocation			
Timepoints	3 + months post-last taxane exposure	Baseline	0	EXP 4 weeks (Tango midpoint)	EXP 8 weeks (Tango end)	EXP 12 weeks (1-month follow up)	6-month follow up period, assessed weekly
ENROLLMENT:							
Eligibility screen	x						
Informed consent	x						
Allocation			x				
ASSESSMENTS:							
Adverse events (including falls)		x^†^		x	x	x	x
Neuropathy (primary outcome Aim 1)		x^†^		x	x	x	x
TUG-Cog (primary outcome Aim 2)		x		x	x	x	
CTCAE		x^†^		x	x	x	
Pain		x^†^		x	x	x	
Fatigue		x^†^		x	x	x	
GAD-2		x		x	x	x	
PHQ-2		x		x	x	x	
SF-36		x		x	x	x	
Satisfaction with intervention				x	x		
Activity outside of study tracking		x^†^		x	x	x	x
Intrinsic motivation				x	x		
Postural control during silence (QEC)		x^†^		x	x	x	
Postural control during music listening (QECm)		x^†^		x	x	x	
TUG		x		x	x	x	
TNSr+		x		x	x	x	
MiniBEST		x			x		
6mwt (EMG, IMUs)		x			x		
Upper extremity function		x		x	x	x	
Goal attainment (COPM)		x			x	x	
Blood-based biomarkers		x			x		
Cognitive load (EEG)		x		x	x	x	

† indicates a measure was repeated 3 times

**Table 2 T2:** SPIRIT report of intervention effect outcome measures for CON group.

	Study Period							
	Enrollment		Allocation	Post-Allocation				
Timepoints	3 + months post-last taxane exposure	Baseline	0	CON 4 weeks (post-SOC)	CON 8 weeks (Tango midpoint)	CON 12 weeks (Tango end)	CON 16 weeks (1-month follow up)	6-month follow-up period, assessed weekly
ENROLLMENT:								
Eligibility screen	x							
Informed consent	x							
Allocation			x					
ASSESSMENTS:								
Adverse events (including falls)		x^†^		x	x	x	x	x
Neuropathy (primary outcome Aim 1)		x^†^		x	x	x	x	x
TUG-Cog (primary outcome Aim 2)		x		x	x	x	x	
CTCAE		x^†^		x	x	x	x	
Pain		x^†^		x	x	x	x	
Fatigue		x^†^		x	x	x	x	
GAD-2		x		x	x	x	x	
PHQ-2		x		x	x	x	x	
SF-36		x		x	x	x	x	
Satisfaction with intervention					x	x		
Activity outside of study tracking		x^†^		x	x	x	x	x
Intrinsic motivation					x	x		
Postural control during silence (QEC)		x^†^		x	x	x	x	
Postural control during music listening (QECm)		x^†^		x	x	x	x	
TUG		x		x	x	x	x	
TNSr+		x		x	x	x	x	
MiniBEST		x		x		x		
6mwt (EMG, IMUs)		x		x		x		
Upper extremity function		x		x	x	x	x	
Goal attainment (COPM)		x		x	x	x	x	
Blood-based biomarkers		x		x				
Cognitive load (EEG)		x		x	x	x	x	

† indicates a measure was repeated 3 times

**Table 3 T3:** SPIRIT report of within-session assessments. EMA refers to “Ecological Momentary Assessment”

Session Type	Baseline	Tango Intervetion		SOC (remote in MyCap app)
Timepoints	Before session start (Beg)	Before session start (Beg)	After completing session (End)	Weekly
ASSESSMENTS:				
Adverse events	x^a^	x^a^		
Neuropathy retrospective	x^a^	x^a^	x^b^	x^a^
PRO-CTCAE retrospective	x^a^	x^a^		x^a^
Pain retrospective (24 hours)	x	x		
Fatigue retrospective (24 hours)	x	x		
Neuropathy EMA	x	x	x	
CTCAE EMA	x	x	x	
Pain EMA	x	x	x	
Fatigue EMA	x	x	x	
Postural control during silence (QEC)	x	x		
Postural control during music listening (QECm)	x	x		
Activity outside of study tracking	x	x		x^a^
Satisfaction with session activity as neuropathy treatment			x	
Intrinsic motivation			x^c^	
COLLECTED TO FACILITATE TRIAL MONITORING AND INTERVENTION SHAPING:				
Rating of perceived physical exertion (RPE-P)			x^b^	
Rating of perceived mental exertion (RPE-M)			x^b^	

a Recall period = during the last week, since we last saw you, OR since you last answered these questions (whichever is the shortest time period)

b Recall period = during the activity just performed

c Queried every 2 weeks

**Table 4: T4:** EEG conditions

Condition	Description
Seated, eyes open	Resting data collected while seated. Participants will be instructed to watch a fixation point on a screen in front of them.
Quiet standing, eyes open	Participants will be instructed to stand with their eyes open while viewing a fixation point on a screen in front of them.
Quiet standing, eyes closed	Participants will be instructed to stand with their eyes closed.
Standing, eyes open with music	Participants will be instructed to stand while Tango music is played. They will be instructed to watch a fixation point on a screen in front of them.
Standing, eyes closed with music	Participants will be instructed to stand with their eyes closed while Tango music is played.
Visual oddball	While standing, participants will be instructed to mentally count how many odd stimuli (yellow square in the center of the screen) are present while ignoring the repetitive stimuli (red square in the center of the screen).
Auditory oddball	While standing, participants will be instructed to mentally count the oddball tone (1500 Hz) and ignore the standard tone (1000 Hz).

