###### Barriers to participation:

Participants are asked “To help us understand barriers to participation, if you missed a session, please indicate the reason why you were unable to attend (e.g., schedule conflict, transportation, didn’t feel up to it, forgot).”

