### Statistical analysis

All outcome analyses will be performed on an intent-to-treat basis, and all hypothesis tests will be two-sided and at the 5% significance level or 95% confidence level. Longitudinal linear mixed models will be used to model changes in PROs and dual-task function. Fixed effects will be included for condition, session number within condition, baseline outcome measure, age, diabetes status, physical fitness activity (defined by weekly duration and metabolic equivalents), and number of previous chemotherapy lines. Random effects for subjects and study center will be used to account for within-subject and within-center correlation, and covariance estimated by restricted maximum likelihood. Exploratory Aim 3 will be assessed via causal mediation analysis using marginal structural models. The primary estimand will be the contrast representing the difference in mean change in outcome measure from baseline to week 4 (end of randomized treatment comparison) between treatment groups.

While we expect balance between groups due to randomization, we will adjust for potential confounders including age, body mass index, concurrent medications, and other variables if an imbalance between groups occurs by chance. Pearson’s *R* will be calculated to correlate PROs, functional outcomes, biomechanical outcomes, brain activity, and biomarker outcomes. We use a longitudinal mixed effect model to analyze all outcomes and do not impute missing outcomes. Subjects will be analyzed in the group to which they were randomized regardless of compliance with the assigned intervention. We will evaluate the effect of the number of intervention sessions completed on outcomes.

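### Recall on the pre-session Tango adverse-event form is capped at 7 days, so the form skips the start of a longer absence

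*Protocol article*

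**What the plan says.** Table 3 attaches footnote a to the Adverse events row in the column for the start of a Tango session. The footnote gives the recall period as "during the last week, since we last saw you, OR since you last answered these questions (whichever is the shortest time period".

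The section on adverse event monitoring ties Tango-phase reporting to attendance: "Participants randomized to the EXP arm complete adverse event reporting each time we see them (2x per week) via REDCap". For controls who cross over: "Once these participants engage in the intervention (one-way crossover period) they report adverse events on the same schedule as the EXP group". Tango runs twice a week, 16 sessions over 8 weeks (Interventions; Experimental Intervention).

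Missed sessions are foreseen. Participants are asked, "if you missed a session, please indicate the reason why you were unable to attend", and the Statistical analysis section says "We will evaluate the effect of the number of intervention sessions completed on outcomes".

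Falls have their own wording, with no cap: "How many times have you fallen or felt like you lost your balance since we last saw you". Tables 1 and 2 also schedule adverse events, including falls, at the assessment visits and weekly in the six-month follow-up, but give no recall period there.

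The reports feed safety oversight: "Any nonserious adverse events are reported to the SO in biannual meetings", and "A biannual open report summarizing study progress and safety monitoring data is reviewed by the SO".

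**The concern.** A rule that takes the shortest of three periods suits symptom severity, because a capped window keeps neuropathy and PRO-CTCAE scores comparable from session to session. Adverse events are different. They accumulate, so the window should reach back to the last time the participant was asked. With a 7-day ceiling and a form completed only at attendance, an absence longer than a week leaves some days that this form never asks about. A brief event early in such an absence, for example a short-lived strain after class, might then not reach the form used twice weekly during Tango, nor the safety officer's biannual review of non-serious events.

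**Working it through.** The plan gives no figure to reproduce. The check enumerates the gaps.

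**Inputs.** Recall is the minimum of 7 days, time since last seen and time since last answered (Table 3, footnote a). There are two sessions per week (Interventions). Assumption: the same two weekdays each week, days 0 and *d*, with *d* from 1 to 6. The article does not give the weekdays.

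**Formula.** Let the gap be the days between two attended sessions. Days not asked about = gap − min(7, gap) = max(0, gap − 7).

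| Consecutive sessions missed | Gap (days) | Days not asked about |
|---|---|---|
| 0 | *d* or 7 − *d*: 1 to 6 | 0 |
| 1 | 7 | 0 |
| 2 | 7 + *d* or 14 − *d*: 8 to 13 | 1 to 6 |
| 3 | 14 | 14 − 7 = 7 |
| 4 | 14 + *d* or 21 − *d*: 15 to 20 | 8 to 13 |

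Examples for two missed: with *d* = 2 the gap is 9 or 12, leaving 2 or 5 days; with *d* = 3 it is 10 or 11, leaving 3 or 4.

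**If the weekdays may change from week to week**, the days not asked about become 0 to 5 for one missed, 0 to 11 for two and 2 to 12 for three.

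**Which events can be lost.** An event lasting *L* days is lost only if it starts after the last form and ends more than 7 days before the return. The vulnerable onset time per absence is max(0, gap − 7 − *L*). For *L* = 3 on fixed weekdays, two missed sessions give 0 to 13 − 7 − 3 = 3 days, and three give 14 − 7 − 3 = 4 days. For *L* = 7, the result is 0 up to three missed sessions (14 − 7 − 7 = 0).

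**Order of magnitude, on assumptions only.** The documents give no attendance rate, event duration or event timing. A simulation put 16 sessions on days 1 and 3 of each week, spread onset uniformly over 56 days, and let the week-4 and week-8 visits ask back to the last form. With independent attendance of 90%, 80% or 70%, the share of 3-day events lost was about 0.2%, 0.8% and 2.0%. With clustered absences (lag-1 correlation 0.5) it was about 1.4%, 2.9% and 4.6%. These indicate scale and are not estimates for this trial.

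**After the change.** If recall equals the full gap, days not asked about = gap − gap = 0 for any number of missed sessions.

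**The case against.** The strongest reply is that one footnote in a condensed table is thin evidence of how adverse events are actually asked. The REDCap item is not shown. Table 3 is not a full account of capture: its Adverse events row is blank in the SOC column, although the text describes weekly reporting through MyCap in that period. The adverse-event section itself states no cap, and the falls and outside-activity items are asked back to the last contact. That limits how far the point reaches, but the footnote is the only recall rule the article states for this item, and no longer catch-up for events other than falls is described.

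Other safeguards narrow the gap. Serious events have a separate 24-hour route. An event still present in the last 7 days can be reported. The missed-session question may catch an event that caused the absence. Staff review answers and prompt for clarification, and safety information is reviewed weekly. All of this stands, though none of it states a longer recall.

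The day counts are also conditional, because they need fixed weekdays.

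A reader might infer that the trial under-reports adverse events during Tango, or that safety data differ between arms. The documents do not support either reading. Recall at the assessment visits is not stated and may cover the whole interval. No recall period is given for adverse-event reporting in the SOC period, so the arms cannot be compared on this point. A reader might also infer that falls are missed; the falls question reaches back to the last contact.

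**Conclusion.** The point holds as a minor flaw in one form. As written, footnote a limits the pre-session adverse-event item to 7 days while completion depends on attendance. On a fixed two-day schedule nothing is lost at full attendance or after a single missed session; the form skips 1 to 6 days after two consecutive absences and 7 after three. What can be lost is confined to non-serious events, other than falls and loss of balance, that begin and end within the skipped days. Across the trial the loss may be nil, namely if the visits at Tango midpoint and end (weeks 4 and 8 in EXP, weeks 8 and 12 in CON) ask back to the previous assessment visit. No primary endpoint, estimand, sample size or comparison between arms is touched.

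**What to change.** For the Adverse events row of Table 3 only, replace footnote a with a recall period such as *since you last completed this adverse-event form*, without a cap, and display the date of that form. Keep footnote a for the neuropathy and PRO-CTCAE items, where a capped window is sensible, and leave the falls question as it is.

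The cost is one footnote and one REDCap item, with no added visits or procedures. It needs a written amendment approved by the NIH and IRB (Protocol amendments). Enrolment opened in January 2025 (Trial status), so participants treated before the change keep the 7-day window, and the date of change should be recorded. Recall after a long absence will be less accurate than over one week, but the alternative is not asking about those days on this form.
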